### Outcomes

Measuring the impact of knowledge transfer and exchange (KTE) interventions, such as the evidence service proposed here, poses significant challenges [14]. The ultimate goal of KTE interventions is typically to improve health. However, there is a long chain of potential causal relationships between an evidence service and improved health. For instance, the evidence service may influence the use of research evidence in different stages of the policy-making process, which in turn may influence decisions made by patients and healthcare providers (*e.g.*, healthcare professionals, teams, and institutions), which may in turn influence whether cost-effective programs, services, and drugs get to the patients who need them and have their desired impacts, and which in turn may translate into improved health [15]. Moreover, even the first relationship in this long chain is complicated by the competing influences on the policy-making process, such as institutional constraints within a political system, stakeholder pressure campaigns, values and beliefs held by key decision makers, and external factors such as the state of the economy [16-18]. Similar challenges arise when assessing the impact of KTE interventions, such as guideline-dissemination strategies, on clinical practice and on health [19-21].

Given these challenges, our primary and secondary outcomes for the trial are proxy measures for the use of research evidence in policy making. The primary outcome will be a measure of utilisation that is similar to the one used in a trial of the McMaster Premium Literature Updating Service (PLUS) [12]. Specifically, we will track the mean number of site visits/month/participant across trial groups during each period, that is, the baseline period, intervention period, and crossover period. We will also provide related descriptive measures such as the proportion of users per month in each of the full-serve and self-serve groups; the frequency with which the full monthly update page, systematic review records, and the more detailed documentation for each review (*e.g.*, user-friendly summaries, scientific abstracts, and full-text reports) are accessed; the mean number of minutes per month that participants use the database (with a 'time out' set at 60 minutes); and the number of times the monthly email alerts are forwarded.

Health Systems Evidence will be hosted on a secure server at McMaster University and will require a user login that will be used to accurately track their usage of the database. A user login is necessary because individuals from the MOHLTC do not have a consistent IP address when accessing external websites, which would preclude the collection of utilisation data if the site were hosted without requiring users to login. In addition, requiring user login will partially protect against contamination of the control group. However, we cannot rule out the possibility that individuals in the intervention arm of the study will forward monthly email alerts and full-text systematic reviews that are available only by subscription to individuals in the control arm; however, we will collect data about alert forwarding.

For the secondary outcome, we will use a survey based upon the theory of planned behaviour to measure participants' intention to use research evidence. The theory of planned behaviour is a model of how human action is guided [22,23], and it consists of three variables--attitudes (*i.e.*, beliefs and judgments), subjective norms (*i.e.*, normative beliefs and judgments about those beliefs), and perceived behavioural control (*i.e.*, the perceived ability to enact the behaviour)--that shape the behaviour intentions of people, which is in turn a strong predictor of future behaviour [23-25]. In Figure 1, we outline linkages among the intervention, contextual developments (described above), and theory of planned behaviour constructs and measures.

**Figure 1 F1:**
[figure not shown]
**Linkages among the intervention, contextual developments, and theory of planned behaviour constructs**.

The theory of planned behaviour has been extensively used and tested in the fields of psychology and healthcare. Systematic reviews conducted in the psychology field have demonstrated that the theory explains about 39% of the variance in intention and about 27% of the variance in behaviour [24,25]. A number of studies have demonstrated the feasibility of producing valid and reliable measures of key theory of planned behaviour constructs for use with healthcare professionals [26-28]. A systematic review suggests that the proportion of the variance in healthcare professionals' behaviour explained by intention was similar in magnitude to that found in the broader literature [29]. This successful transfer of the theory from individuals (as studied by psychologists) to healthcare professionals involved in an agency relationship with their patients (as studied by health-services researchers) bodes well for its further transfer to policy analysts and advisors involved in an agency relationship with Ministers and other senior officials.

Using a manual to support health researchers who want to construct measures based on the theory [23], we developed and sought preliminary feedback on a data collection instrument by first assessing face validity through interviews with key informants and then pilot testing it with 28 policy makers and researchers from 20 low-middle income countries who completed it after participating in a KTE intervention [30]. In addition, Boyko *et al. *(2010) found moderate test-retest reliability of the instrument using generalisability theory (*G *= 0.50) [31] when scores from a sample of 37 health-system policy makers, managers, professionals, citizens/consumers, and researchers participating in stakeholder dialogues convened by the McMaster Health Forum were generalised across a single administration, and even stronger reliability (*G *= 0.9) when scores were generalised across the average of two administrations of the tool [30]. In the reliability assessment by Boyko *et al. *(2010), the first administration of the tool immediately followed a McMaster Health Forum stakeholder dialogue, which may have promoted enthusiasm for using research evidence among participants. This likely produced higher measures of intention on the first administration of the tool as compared to the second, resulting in the lower *G *score. Given that we won't be administering the tool in a similar atmosphere of enthusiasm for using research evidence, we are confident in the level of reliability of the tool without two administrations at both baseline and follow-up. We modified the instrument by adding a question to measure the perceived usefulness of the intervention, as well as questions about participant characteristics.

We will administer the instrument during the baseline period, as well as at the end of the six-month intervention period, through a brief online survey that takes approximately 10 minutes to complete. We will use unique identifiers for each participant to ensure their responses to the previous survey are linked for calculations of before-and-after changes in their intention to use research evidence. We will follow up with participants who do not complete the survey once per week for three weeks to minimise the number of participants lost to follow-up.

### Data management and analysis

Data will be entered into SPSS 16.0 (IBM Corporation, Somers, NY) after all data collection has been completed. Analyses will be conducted by two members of the research team (SH and [name]), and during the analysis, neither they nor other study investigators will have access to the key linking the participants to their unique identifiers.

We will treat both outcome measures as continuous variables and analyse the change in these measures over time using a two-way mixed-effects linear repeated-measures analysis of variance (ANOVA), with the interaction of intervention by time as the main feature of interest. In addition, we will control for four variables--past workshop attendance, position (policy analyst, senior policy analyst, or senior policy advisor), branch within the division (of which there are six), and number of years working at the MOHLTC--using analysis of covariance. Given the likelihood that the distribution of the outcomes will be skewed, we will transform the data where necessary and possible, which may include adjusting the time period for which we calculate the mean number of site visits/participant (*e.g.*, calculating the mean over two months) if there are insufficient data for analysis. Moreover, as part of a secondary analysis, we will assess whether there is an interaction between each of these variables (entered as a fixed factor) and the outcome measures. We will also qualitatively compare the number of participants in the intervention and control groups that do not complete the follow-up survey and assess whether their baseline characteristics can help to explain their loss to follow-up.

For all analyses, we will use the intention-to-treat principle and report 95% confidence intervals; *p *values equal to or less than .05 (two-tailed) will be considered significant. For the primary outcome measure (mean number of site visits/month/participant), missing data are irrelevant because it is a naturalistic measure. For the secondary outcome measure (obtained through the survey), missing data can be taken into account through the use of a mixed-effects model.

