## Methods/design

We will conduct this trial using a sequential explanatory mixed-methods design, [13] beginning with the randomised controlled trial (RCT) and then following up with a qualitative process study to explore the RCT findings in greater depth. For an initial two-month baseline period, all participants will receive the self-serve evidence service. For the following six-month period, the intervention group will receive the full-serve evidence service and the control group will continue to receive the self-serve evidence service. For a final two-month period, both groups will receive the full-serve evidence service. This protocol received ethics approval from the Hamilton Health Sciences/Faculty of Health Sciences Research Ethics Board at McMaster University (project number 10-267).

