### Randomisation

Participants will be randomised using a stratified design. After completing the baseline questionnaire during the two-month baseline period, participants will be allocated to strata based on past workshop attendance (yes or no) and their position (policy analyst, senior policy analyst, or policy advisor). This two-layer stratification will produce six strata. Participants will be randomised after all those who consent to participate in the trial have completed the baseline questionnaire. We will assign a unique participant ID number to each participant and then provide the list of IDs to a biostatistician external to the research team who will conduct the randomisation and keep a log to provide a clear audit trail. The biostatistician will then communicate directly with a knowledge broker external to the research team who will be generating the email alerts and with the website server administrator at McMaster University who will be establishing which participants get access to which evidence service. The participants and investigators will be blinded to group assignment.

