### Statistical precision

Given a fixed sample size of at least 148 policy analysts and advisors in the division, a sample-size calculation is not relevant. Instead, we have calculated the level of statistical precision that we can expect given our fixed sample size. We had no mechanism to estimate the intraclass correlation coefficient (ICC) for measurements of the primary outcome for individuals over time. Therefore, we calculated estimates of statistical precision for ICCs of .2, .3, .5, .7, and .8 based on a six-month trial period with 80% power; an estimated standard deviation of 1.0; significance of .05; and 74 participants per study group (total n = 148, which does not include the as yet undefined number of senior policy advisors). Assuming the primary outcome data will be collected from all 148 participants at baseline and at six follow-up points (one per month), the time-averaged detectable difference (in standard deviation units) between the two groups is at best 0.27 (ICC = .2), which increases with successively greater ICCs to 0.30 (ICC = .3), 0.35 (ICC = .5), 0.40 (ICC = .7), and 0.42 (ICC = .8).

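### The primary test of site visits is an intervention-by-time interaction with no adjustment for each participant's own baseline visits: valid, but inefficient if the within-person correlation is low

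*Protocol article*

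**What the plan says.** All from the protocol article.

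- **Methods/design:** "For an initial two-month baseline period, all participants will receive the self-serve evidence service". The services diverge only afterwards.
- **Outcomes:** for the primary outcome, "we will track the mean number of site visits/month/participant across trial groups during each period, that is, the baseline period, intervention period, and crossover period". A baseline value on the outcome's own scale therefore exists for each participant, taken over two months.
- **Randomisation:** "participants will be allocated to strata based on past workshop attendance (yes or no) and their position".
- **Data management and analysis:** both outcomes are to be analysed as changes from one time to the next. The model is a "two-way mixed-effects linear repeated-measures analysis of variance (ANOVA), with the interaction of intervention by time as the main feature of interest". They add that "we will control for four variables--past workshop attendance, position (policy analyst, senior policy analyst, or senior policy advisor), branch within the division" and "number of years working at the MOHLTC--using analysis of covariance". Baseline visits are not in the list. The same section treats missing data as not applicable to site visits.
- **Statistical precision:** the figures are computed "Assuming the primary outcome data will be collected from all 148 participants at baseline and at six follow-up points (one per month"), with SD 1.0, 74 per group, 80% power and ICCs of .2, .3, .5, .7 and .8. The detectable differences are 0.27, 0.30, 0.35, 0.40 and 0.42 SD. The section says the ICC could not be estimated.

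**The concern.** The section names the model, the effect to be tested and the covariates, so this is a stated choice and not a detail left open. Baseline must be one of the time levels. If the service had a constant effect over the six months, an interaction among those months alone would be zero and could not test the service.

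With a separate arm effect at baseline, the one-degree-of-freedom interaction is the arm difference in (follow-up mean minus baseline mean). It subtracts baseline with weight 1. Under the protocol's single-ICC model the efficient weight is smaller, and much smaller when the ICC is low, so subtracting the whole baseline adds noise to the estimate.

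The four listed variables do not obviously make up for this. They are fixed within a person. Entered as main effects only, they explain between-person variation, which the interaction has already removed.

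What is at stake is power. The sample is fixed by the size of the division, so recruiting more people cannot recover precision that the analysis gives away.

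**Working it through.** **Inputs** (Statistical precision section): n = 74 per arm, SD 1, two-sided .05, one common correlation r (the ICC), six monthly follow-ups. Baseline: two months averaged (Methods/design and Outcomes), with a single value as the alternative. SD is taken as equal before and during the intervention.

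**Variances per person**
- Follow-up mean: F = (1 + 5r)/6.
- Baseline mean: B = (1 + r)/2 for two months, or 1 for a single value. Its covariance with the follow-up mean is r.
- Change contrast: F + B − 2r.
- Baseline-adjusted: F − r²/B. The efficient weight on baseline is r/B.
- Detectable difference at 80% power: 2.80 × √(2V/74).

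**The protocol's own figure.** V = F alone gives 0.266/0.297/0.352/0.399/0.420, which matches all five stated values. The stated precision is thus for a comparison of six-month means that makes no use of baseline.

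**One case in full: r = .2, two baseline months, difference 0.27.**
- F = 2.0/6 = 0.333; B = 1.2/2 = 0.60; efficient weight = 0.2/0.60 = 0.33.
- Change: V = 0.333 + 0.60 − 0.40 = 0.533; SE = √(2 × 0.533/74) = 0.120; 0.27/0.120 = 2.25; power 61%.
- Adjusted: V = 0.333 − 0.04/0.60 = 0.267; SE = 0.085; 0.27/0.085 = 3.18; power 89% (88.5% by noncentral t, 88.9% by the normal approximation).
- Variance ratio 0.267/0.533 = 0.50. For 80% power the change contrast needs 115 per arm and the adjusted analysis 58.

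**All ICCs, at the protocol's own detectable differences**

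| ICC | .2 | .3 | .5 | .7 | .8 |
|---|---|---|---|---|---|
| Difference (SD) | 0.27 | 0.30 | 0.35 | 0.40 | 0.42 |
| **Two-month baseline mean** | | | | | |
| Power, change | 61% | 76% | 96% | 100% | 100% |
| Power, adjusted | 89% | 93% | 99% | 100% | 100% |
| Detectable, change | 0.336 | 0.315 | 0.266 | 0.206 | 0.168 |
| Detectable, adjusted | 0.238 | 0.243 | 0.230 | 0.192 | 0.161 |
| Variance ratio, adjusted/change | 0.50 | 0.60 | 0.75 | 0.87 | 0.92 |
| **Single baseline value** | | | | | |
| Power, change | 39% | 52% | 79% | 98% | 100% |
| Power, adjusted | 85% | 89% | 96% | 99.7% | 100% |
| **Omnibus interaction, seven time levels (6 df)** | | | | | |
| Power | 20% | 27% | 51% | 89% | 99% |

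The omnibus row assumes a constant effect and uses the noncentral F with λ = (74/2) × d² × (6/7)/(1 − r). At r = .2, λ = 37 × 0.0729 × 0.857/0.8 = 2.89.

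**Sensitivity to the equal-SD assumption.** The protocol gives only one SD. As an illustration, assume a monthly baseline SD of half the follow-up SD. With two baseline months, change against adjusted power becomes 86.5% against 88.5% at ICC .2, and 93% against 93% at .3. With one baseline value it is 75% against 85%, and 85% against 89%.

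**Covariates.** In a complete simulated data set (148 people, seven times, random intercept), the interaction estimate and SE were 0.34999 (0.13201) without person-level covariates and identical with them as main effects. Adding covariate-by-time terms gave 0.38149 (0.13647). Comparing follow-up means with baseline as a covariate gave an SE of 0.105.

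**The case against.** The strongest reply is that nothing here is wrong. Under randomisation the interaction is an unbiased comparison with correct type I error, and it matches the abstract, which describes the outcome as running from baseline to the end of the intervention period. This stands: the point is efficiency, not validity.

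A reader might infer from the single-baseline or omnibus figures that the trial has about 40% power, or even 20%. The documents do not support that as the headline. The baseline period lasts two months and the outcome is a mean over each period, so the two-month figures are the fairer reading. On those, the planned contrast beats the stated precision at ICC .5 and above and is close to it at .3 (0.315 against 0.30). Whether the test has one or six degrees of freedom is not stated.

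A reader might also infer that the four covariates can never affect the test. That holds only for main effects with complete data. The protocol says just that analysis of covariance will be used, and does not say whether covariate-by-time terms enter.

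Nor do the documents say what effect the authors hope for. The 0.27 to 0.42 SD are differences detectable with a fixed sample, and serve here only as a benchmark.

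Finally, how the model is parameterised could be left to an analysis plan, and a model with a common baseline mean would remove the problem. But a two-way model on change, with the interaction as its focus, points to a free arm effect at baseline, and the listed covariates omit baseline visits.

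**Conclusion.** The point holds as a matter of efficiency. With a two-month baseline mean, adjustment gains about 28 points of power at ICC .2 (61% to 89%), 17 at .3 and 3 at .5, and essentially nothing at .7 to .8. At ICC .5 the gain is material only with a single baseline value (79% to 96%) or if the interaction is tested as an omnibus (51%). At .2 and .3 the change contrast is less precise than ignoring baseline altogether (0.336 against 0.266 SD; 0.315 against 0.297 SD).

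These sizes rest on compound symmetry, 74 per arm, and equal SD before and during the intervention. They shrink, possibly to almost nothing, if baseline visits vary less. The true ICC is unknown. What does not depend on its value within this model is that the adjusted analysis is never materially worse, since it gives up only one degree of freedom. That makes the change worth making without knowing the ICC.

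**What to change.** In Data management and analysis, define the primary analysis of site visits as the arm difference in each participant's visit rate over the six intervention months. Enter that participant's two-month baseline visit rate as a covariate, on the same scale or transformation as the outcome, alongside workshop attendance, position, branch and years at the MOHLTC.

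Equivalently, keep the repeated-measures model, give the arms a common baseline mean, and test one arm contrast averaged over the six intervention months. Keep the monthly arm-by-time pattern as a secondary description.

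The cost is one degree of freedom and a change of wording. No further participants or measurements are needed, because the baseline visits are already logged.

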**Methods/design:**

We will conduct a two-arm randomized controlled trial (RCT), along with a follow-up qualitative process study in order to explore the findings in greater depth. For the RCT, all policy analysts and policy advisors (n = 168) in a single division of the MOHLTC will be invited to participate. Using a stratified randomized design, participants will be randomized to receive either the "full-serve" evidence service (database access, monthly e-mail alerts, and full-text article availability) or the "self-serve" evidence service (database access only). The trial duration will be ten months (two-month baseline period, six-month intervention period, and two month cross-over period). The primary outcome will be the mean number of site visits/month/user between baseline and the end of the intervention period. The secondary outcome will be participants' intention to use research evidence. For the qualitative study, 15 participants from each trial arm (n = 30) will be purposively sampled. One-on-one semi-structured interviews will be conducted by telephone on their views about and their experiences with the evidence service they received, how helpful it was in their work, why it was helpful (or not helpful), what aspects were most and least helpful and why, and recommendations for next steps.

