Third, we developed the format for monthly email alerts, which (in tabular format) identifies new additions to Health Systems Evidence and describes the type of review, type of question addressed, health-system arrangement or implementation strategy addressed, and title of the review. A hypertext link for each review enables policy makers to view the availability of (and links to) user-friendly summaries, scientific abstracts, and the full-text review. A hypertext link to the online Health Systems Evidence webpage enables policy makers to view additional information about these same recent database additions, including the last year searched, quality rating, the countries in which included studies were conducted, and the complete citation. (Electronic newsletter width restrictions precluded having all fields presented in the monthly email alerts.)

Our goal is to evaluate whether (and how and why) a full-serve evidence service increases the use of synthesised research evidence by policy analysts and advisors in the MOHLTC as compared to a 'self-serve' evidence service. The full-serve evidence service comprises database access (an effort to facilitate policy makers' efforts to 'pull' in research when they need it), monthly email alerts about new additions to the database (a 'push' effort), and full-text article availability (an additional effort to facilitate pull). A systematic review found that simply providing information (in the form of clinical-practice guidelines) can change clinical behaviour,[11] which leaves us reasonably confident that we have the potential to achieve an increase in evidence use among health-system policy makers. Moreover, the results of a cluster randomised trial indicate that a full-serve evidence service increased practicing clinicians' utilisation of evidence-based information from a digital library [12].

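### The named primary test, an intervention-by-time interaction with no stated time levels or contrast, is not tied to the time-averaged difference in mean use that the objective and the precision statement concern

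*Protocol article*

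**What the plan says.** The Background states the goal as finding out whether (and how and why) "a full-serve evidence service increases the use of synthesised research evidence by policy analysts and advisors". The Abstract says: "The primary outcome will be the mean number of site visits/month/user between baseline and the end of the intervention period". The Outcomes section describes a mean per period, with three periods: baseline, intervention and crossover.

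Data management and analysis then names, for both outcomes, a two-way mixed-effects linear "repeated-measures analysis of variance (ANOVA), with the interaction of intervention by time as the main feature of interest". It states no time levels, degrees of freedom or contrast. It promises 95% confidence intervals for all analyses, and p "values equal to or less than .05 (two-tailed) will be considered significant". If data are too sparse, averaging visits over two months is offered as an adjustment.

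Statistical precision is "based on a six-month trial period with 80% power; an estimated standard deviation of 1.0", with "74 participants per study group (total n = 148" and measurements "at baseline and at six follow-up points (one per month". It reports time-averaged detectable differences of 0.27, 0.30, 0.35, 0.40 and 0.42 SD at ICC .2, .3, .5, .7 and .8.

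**The concern.** The objective and the precision statement both concern one number: how much higher mean use is in the full-serve arm. The interaction tests that number only if time has two levels, baseline and intervention. With more levels it asks whether the arm difference is the same at every time point. It then spreads its power over every possible monthly pattern and has no direction.

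Two things are at stake. A sustained increase of the size the article says it can detect might be missed. And a significant result might be reported as increased use when the test shows only that the arms' time courses differ. Because the sentence leaves the coding open, two analysts could also run different primary tests from it.

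**Working it through.** **Inputs.** From Statistical precision: 74 per arm, SD 1.0, 80% power, alpha .05 (two-tailed, from Data management and analysis), one baseline and six monthly points, ICC ρ from .2 to .8. Assumed: compound symmetry, normal data, no covariates, time categorical.

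**1. Reproduce the stated precision.** For a difference in the mean of m follow-up points, d = (1.960 + 0.842) × √[2(1 + (m − 1)ρ)/(74m)]. With m = 6 and ρ = .5, d = 2.802 × √(7/444) = 0.352. Across the five ICCs, d = 0.266, 0.297, 0.352, 0.399 and 0.420, which match all five stated values. With m = 7 the first two are 0.258 and 0.291, which do not match. The stated precision is therefore for a one-degree-of-freedom difference in the six-month mean, not for an interaction.

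**2. Power of the monthly interaction.** With seven time levels the test is F on 6 and 6 × 146 = 876 degrees of freedom. Its noncentrality is λ = (74/2) × Σ(δ_t − mean δ)²/(1 − ρ), where δ_t is the arm difference at time t. For a sustained shift δ after baseline, the sum is (6/7)δ². At ρ = .5, λ = 37 × (6/7) × 0.3518²/0.5 = 7.85, and power is 51.8% (52.2% in 10,000 simulated trials).

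**3. Two one-degree-of-freedom comparators, same δ.**
- Change contrast (six-month mean minus baseline): λ is the same, because δ²/[(2/74)(1 − ρ)(1 + 1/6)] = 37 × (6/7)δ²/(1 − ρ), but it is tested on 1 degree of freedom.
- Six-month mean adjusted for baseline: variance per person v = (1 + 5ρ)/6 − ρ², power = Φ(δ/√(2v/74) − 1.96). At ρ = .2, v = 0.293 and power is 85%.

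| ICC | δ | 6-df interaction | 1-df change | Loss (points) | Baseline-adjusted mean |
|---|---|---|---|---|---|
| .2 | 0.266 | 19.2% | 38.7% | 19.5 | 84.8% |
| .3 | 0.297 | 26.8% | 51.6% | 24.7 | 88.6% |
| .5 | 0.352 | 51.8% | 79.9% | 28.1 | 96.0% |
| .7 | 0.399 | 88.5% | 98.4% | 9.8 | 99.7% |
| .8 | 0.420 | 98.9% | >99.9% | 1.0 | >99.9% |

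(Losses are from unrounded powers.)

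**4. Other codings of time.**
- Two levels (baseline mean, intervention mean): the interaction is the change contrast, and nothing is lost.
- Two separate baseline months plus six (eight levels): interaction power is 30.6%, 43.8%, 77.5%, 99.0% and about 100%, a loss of 0 to 31.5 points.
- Two-month bins (one baseline bin, three follow-up bins): 42.9%, 58.6%, 88.7%, 99.8% and about 100%, against 59.9%, 75.2%, 95.9%, about 100% and about 100% for the 1-df contrast.

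**5. What a rejection means (seven levels, ICC .5).**
- No effect in any month: the interaction rejects in 5.1% of simulated trials.
- Zero net gain, with the arm difference drifting linearly from +0.2 to −0.2 SD over the six months: Σ(δ_t − mean δ)² = 0.112, λ = 37 × 0.112/0.5 = 8.29. The interaction rejects in 53% of simulated trials, the 1-df contrast in 5%. At ±0.3 SD the figures are 91% and 5%. Both drifts are assumed.
- Decaying effect with monthly differences 2δ × (6, 5, 4, 3, 2, 1)/7, mean still δ (assumed shape): interaction 95%, change contrast 80%. The baseline-adjusted mean depends only on the six-month average, so it stays at 96%.

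**The case against.** The strongest reply is that monthly levels are not stated. The Abstract and Outcomes section describe means over periods, and a two-level factor would make the interaction exactly the right test. The promise of confidence intervals and two-tailed p values also sits more easily with a single contrast. The survey outcome, measured twice, already gives a 1-df interaction, and time coding is often left to an analysis plan. This stands to the extent that monthly coding is an inference. It rests on the monthly points in the precision section and on a two-month fallback that implies a shorter default. It does not remove the point, because the article itself pairs a named test with a precision statement for a different quantity.

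A reader might infer more: that the plan definitely uses a 6-df test, that it loses 28 points of power in general, or that it rejects too often when the service does nothing. The documents support none of these. The 28 points arise only where the change contrast has 80% power, which at the article's own differences is ICC .5, and the ICC is unknown. With randomised arms and baseline as a time level, equal arm differences throughout means no effect in any month, and there the error rate is 5%. Rejecting with zero net gain needs full-serve use to fall below control in some months. A novelty peak that merely fades still has a positive mean. For such a decaying effect the interaction can beat the change contrast.

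The change score is also a weak remedy at low ICC: 39% power at ICC .2, against 85% with baseline adjustment.

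**Conclusion.** The point holds in a limited form. The article names a primary test without fixing the time levels or the contrast, and does not tie it to the time-averaged difference that its objective and its 80% power statement concern. Under monthly coding, a sustained increase of the stated detectable size would be found with about 19% to 99% power depending on the ICC: below 80% at ICC .2, .3 and .5, above it at .7 and .8. The cost relative to a 1-df change contrast is 1 to 28 points. These figures assume compound symmetry, normality, no covariates and a constant shift. Under two-level coding there is no loss. Whatever the power, a significant interaction across several months would not by itself establish that mean use rose.

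**What to change.** In Data management and analysis, state the time levels and name one primary 1-df contrast with its 95% CI: the arm difference in mean monthly visits over the six intervention months, preferably adjusted for each participant's baseline visits, otherwise minus baseline. Baseline visits are not among the four covariates now listed, so they would be added. Under the assumptions above, the adjusted form reaches at least 80% power at every ICC for the stated differences, so the precision section can stand. Report the monthly arm-by-time interaction as a secondary description of the time course.

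The cost is a sentence or two of text and one contrast; no new data are needed. The small downside is that a transient early effect is averaged in the primary test, though it stays visible in the monthly profile.
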